### Safety

To guarantee that the ACE operation is standard and safe, the acupuncturists in this study should pay attention to the following: (1) ensure the operation is strictly aseptic to prevent infection; (2) catgut should not be embedded in adipose tissue that could prevent fat liquefaction; (3) catgut should not be exposed to the body surface to prevent infection; (4) master the angle and depth of the embedding in order to avoid injury to the internal organs, great vessels, nerves, etc.; (5) acupoints can’t be wet for 24 h after embedding; (6) inform patients that they may experience soreness, distension, and numbness at the acupoints for one or two days, and possibly more than three to five days.

### Management of adverse events

ACE therapy may lead to different AEs, such as fainting during operation, subcutaneous hematoma, allergy, infection, severe pain, etc. Any AEs experienced by participants should be reported to the researchers. After confirming the validity of the AEs by an evaluator, the acupuncturists will immediately stop the treatment procedure and deal with the AEs. All AEs, as well as management of the AEs, will be carefully recorded during treatment and follow-up phases.

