### Sham ACE group

Patients in the sham ACE group will undergo a similar procedure to the verum ACE group except that nothing will be put into the catgut embedding needles before operation; thus, no catgut will be left under the patients’ acupoint tissue after needle extraction. The prescription of acupuncture will also be the same as that in the verum ACE group.

In the current study, all patients will be treated separately to avoid influencing each other. Both groups will be treated under the same conditions by acupuncturists, who will receive special training before participation in the study. During the entire ACE operation process, the acupuncturists and assistants will not talk about details.

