### Quality control

Acupuncturists, assistants, data collectors, and statisticians who participated in the study should abide by the rules and regulations. Before the study, each researcher took basic study training to understand the design, purpose, and basic information about this research. The acupuncturists should have at least 3 years of practical acupuncture experience, and they also should be familiar with the operation process and be able to cope with any possible AEs. Data collectors are responsible for saving and managing various data, and strictly proofread data. Patient withdrawals and AEs during the study will be recorded in detail. Statisticians will be fully responsible for data management and statistical analysis. Regular team meetings will be held and fully documented.

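### As written, an adverse event is confirmed by an evaluator before the acupuncturist stops and treats, which is the wrong order for an acute event during a session

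*Protocol article*

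**What the plan says.** Management of adverse events opens with a list of what the treatment may cause: "ACE therapy may lead to different AEs, such as fainting during operation, subcutaneous hematoma, allergy, infection, severe pain, etc". It then sets a reporting rule with no exceptions: "Any AEs experienced by participants should be reported to the researchers". The response follows: "After confirming the validity of the AEs by an evaluator, the acupuncturists will immediately stop the treatment procedure and deal with the AEs". The section ends by requiring that events and their management be recorded during treatment and follow-up.

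Two other sections bear on the point. Safety lists precautions for the operator and includes the advice to "inform patients that they may experience soreness, distension, and numbness at the acupoints for one or two days". Quality control asks for acupuncturists with at least 3 years of practice and adds that "they also should be familiar with the operation process and be able to cope with any possible AEs".

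**The concern.** The sentence puts the evaluator's confirmation ahead of two actions, stopping the procedure and dealing with the event. The word *immediately* takes effect only once confirmation has been given. That order suits a complaint raised between weekly visits, where someone has to judge whether soreness is the expected after-effect or something more. It does not suit a patient who faints while being needled. There the needling should cease and care should begin first, and confirmation can come later because it serves classification and the record.

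What is at stake is patient safety during a session. A response rule should be safe when followed to the letter, and this one is not safe for an event that its own section names.

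**Working it through.** There is no figure to reproduce and no arithmetic to run, because the point depends on no rate, sample size or significance level. The check is to read the response sentence against every other part of the article that might change its order or scope.

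1. **Scope of the sentence.** The preceding list includes fainting during the operation, which is in-session by its own wording. The reporting sentence in between covers adverse events of any kind. Nothing separates acute events from later complaints, so the sequence applies to fainting.

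2. **What is stopped.** The phrase could mean the session in progress or the remaining sessions. The article favours the first meaning. The section headed Operation procedures of ACE describes the needling itself, and the Sham ACE group section uses *procedure* for what is done with the needle. The Interventions section calls the eight weekly sessions a *course*. If the second meaning were intended, the section would contain no instruction to stop a session for an event that it lists.

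3. **Other sections that might supply a different order.**
   - Dropout criteria: severe events are a ground for leaving the trial. Nothing is said about what happens at the bedside.
   - Blinding: severe allergy, serious infection and uncontrolled pain permit allocation to be revealed. This concerns unblinding, not stopping or treating.
   - Operation procedures of ACE: describes a normal session, with an acupuncturist and an assistant present. There is no emergency step.
   - Safety: precautions and advice to patients. There is no rule for responding.
   - Quality control: competence to handle adverse events. There is no order of steps.
   - Data management and monitoring: the committee may modify or terminate the trial. This is a trial-level power.

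4. **Result.** Confirm first, then stop and treat, is the only response order in the article, and it covers at least one event for which it is wrong.

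5. **Size.** The article gives neither the frequency of in-session events nor the time an evaluator needs to confirm one. Any expected number of patients or length of delay would be invented, so none is given. Counting the event types in the list would not help, because the list is open-ended and a count of types measures neither frequency nor harm.

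**The case against.** The strongest reply is that this is loose wording in a condensed article. The section moves from participants' reports to validation, which reads like an administrative pathway for complaints. The stress on immediacy shows that prompt stopping was the aim. The acupuncturists must "be able to cope with any possible AEs", with no condition of prior confirmation. Detailed emergency handling is usually left to the full protocol or site procedures, which are not shown here.

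Much of this stands. It makes actual delay unlikely and keeps the point small. It does not make the sentence right, because the article does more than omit detail: it states a sequence, and that sequence fails for an event the section itself names.

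Three stronger readings are tempting, and the article does not support them.

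- A reader might infer that the acupuncturist is barred from acting until an evaluator arrives. The text sets an order but contains no prohibition.
- A reader might infer that the evaluator is the blinded outcome assessor, away from the treatment room, so that a long delay is built in. The section does not define the evaluator and does not say where this person is.
- A reader might enlarge the point with the hazards in the Safety section, where operators are told to "master the angle and depth of the embedding in order to avoid injury to the internal organs, great vessels, nerves, etc". Those appear as reasons for a precaution and are not among the listed adverse events. Allergy and severe pain are listed, but placing them within a session is a clinical assumption. Fainting is enough to carry the point.

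**Conclusion.** The point holds as a minor matter of patient safety. Read literally, the article puts confirmation before stopping and treating for a set of events that includes one that is in-session by its own wording, and no other section corrects this. The conclusion rests on two things: that the sentence applies to the whole list before it, and that the procedure to be stopped is, or includes, the session under way.

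It does not show that the investigators chose to delay first aid or that any patient has been or will be harmed. Practitioners of the required experience would probably act at once. Confirming first is not an error for every kind of event, since checking a complaint of expected soreness is reasonable. The estimand, the analysis, the sample size and the error rates are unaffected. The change is optional but worth making.

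**What to change.** Reword the response sentence in Management of adverse events along these lines:

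*If an AE is suspected during a session, the acupuncturist stops the procedure and treats the patient at once; the evaluator then confirms, grades and records the AE.*

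Add no requirement that complaints arising between sessions be confirmed before sessions are held back. Such a rule could delay withholding treatment after a reported infection or allergy. How each event is treated clinically remains for the investigators.

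The cost is one reworded sentence and a short instruction to the acupuncturists. Under Ethics approval, an amended protocol goes to the Ethics Committee and takes effect only with its consent. Trial status describes the trial as recruiting, so the change would reach patients still to be treated. No new data, sample size change or analysis change is needed.

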### Quality control

Acupuncturists, assistants, data collectors, and statisticians who participated in the study should abide by the rules and regulations. Before the study, each researcher took basic study training to understand the design, purpose, and basic information about this research. The acupuncturists should have at least 3 years of practical acupuncture experience, and they also should be familiar with the operation process and be able to cope with any possible AEs. Data collectors are responsible for saving and managing various data, and strictly proofread data. Patient withdrawals and AEs during the study will be recorded in detail. Statisticians will be fully responsible for data management and statistical analysis. Regular team meetings will be held and fully documented.

### Ethics approval

This study was approved by the Chinese Clinical Trial Registry. The registration number of this trial is ChiCTR1800020248. In addition, the study protocol was approved by the Ethics Committee of Shenzhen Traditional Chinese Medicine Hospital. Prior to start of the study, patients will be informed about the potential risks of the study. Patients voluntarily participate in the study with informed consent. If the protocol needs to be amended, all the materials on trial will be reported to the Ethics Committee, and the amended protocol can only be implemented after consent is acquired.

### Data management and monitoring

The research associates will record the information on the CRFs and verify that the data is fully, swiftly, and accurately collected. The private information and medical records of patients, including their name, phone number, and ID number, will be anonymous to ensure confidentiality. All the research documents will be kept in specialized cabinets and preserved for at least 5 years after publication.

In addition, a data monitoring committee is established consisting of experienced experts in the Good Clinical Practice Department of the Shenzhen Traditional Chinese Medicine Hospital to periodically review the progress of the trial and monitor collection of the data, allocation concealment, etc. The modification or termination of the trial can be performed by the committee. The data monitoring committee is independent from the sponsor and has no conflict of interest.

## Discussion

It is noteworthy that ACE is extensively applied for weight loss. Although previous studies have shown that ACE might be effective in improving overweight, high-quality trials with rigorous design are still urgently required to assess the effects of ACE on obesity [29]. The results of the present study may contribute to a better understanding of how ACE exerts its potential therapeutic effects on obesity.

Recently, increasing attention has been paid to the visceral fat of obesity, which is related to energy storage, and is considered as an endocrine and paracrine organ, influencing a number of metabolic processes by releasing cytokines and bioactive mediators [30–33]. Body weight can be adjusted by cytokines and mediators. Thus, VFA is a significant indicator for estimating metabolic risk in obese populations [34, 35]. In previous studies, however, the influence of ACE on obesity was mainly assessed by BMI or WC, and a limited number of studies have assessed those influences in relation to VFA. Hence, evaluation in this study is done according to both standard obesity-related indices (BMI, WC, etc.) and VFA in order to clearly illuminate the effects of ACE on obesity.

The purpose of this study is to compare measurement changes after 2 months of treatment with three different intervention methods: verum ACE, sham ACE, and no intervention (WLC group). Several studies [36, 37] have indicated that a sham-controlled design could separate specific and non-specific effects, which may play a pivotal role in evaluating the effectiveness of treatment. Thus, the ACE and sham ACE treatments are both applied to investigate the anti-obesity effects in this study. The sham ACE treatment involves only needle piercing into the acupoints without catgut being fixed; the rest of the procedure is the same as in the ACE group. Thus, it can successfully blind patients and estimators; as a result, it can minimize the placebo effect. In addition, as far as non-specific effects (sham ACE versus no intervention) and bias caused by psychological influences, the third group without any intervention is considered to avoid the placebo effects of group allocation or patients’ beliefs on weight loss. A possible limitation of this trial is that compliance might be difficult for participants due to the long interval from the end of the 2 months of treatment to the follow-up at 3 months. Several actions, such as phone interview, should be taken to improve compliance.

The design and methodological rigor of this trial may hopefully provide consolidated evidence regarding the efficacy and safety of ACE for treating obesity, through collecting valuable and high-quality data, and also contribute to future research in ACE therapy.

## Trial status

This trial is currently recruiting patients. The trial began recruitment on January 1, 2019 and is anticipated to be completed on December 31, 2021. The version number and date of the protocol are v1.0, and October 25, 2018, respectively.

## Data Availability

The full data from this study will be available upon reasonable request after completion of the study.

## Abbreviations

ACC: American College of Cardiology
ACE: Acupoint catgut embedding
AE: Adverse event
BFP: Body fat percentage
BMI: Body mass index
BP: Blood pressure
CVD: Cardiovascular disease
FDA: Food and Drug Administration
GHO: Global Health Observatory
HC: Hip circumference
HDL: High-density lipoprotein
HR: Heart rate
MRI: Magnetic resonance imaging
NHLBI: National Heart, Lung and Blood Institute
NIH: National Institutes of Health
RCT: Randomized controlled trial
SD: Standard deviation
SFA: Subcutaneous fat area
STRICTA: Standards for Reporting Interventions in Clinical Trials of Acupuncture
T2D: Type 2 diabetes
TC: Total cholesterol
TG: Triglyceride
VFA: Visceral fat area
WC: Waist circumference
WHO: World Health Organization
WHOQOL: World Health Organization Quality of Life
WHR: Waist:hip ratio
WT: Waiting list
